## Abstract

**Introduction:**

Unhealthy eating behaviour is a major contributor to obesity and related diseases and is associated with a behavioural bias to approach rather than avoid desired foods, as measured with reaction time tasks. Approach-avoidance interventions (AAIs) have been proposed as a way to modify food evaluations and help people to eat in accordance with their dietary goals. Mobile implementations of AAI might be easily accessible, low threshold interventions, but their effectiveness has not been established yet.

**Methods and analysis:**

Participants who aim to change their eating behaviour are randomised to intervention or control groups. They complete six sessions of a smartphone-based AAI, in which they push (ie, avoid) or pull (ie, approach) personalised food images. Intervention group participants always avoid foods that they personally want to eat less often and approach foods that they personally want to eat more often. In the control group, images are paired equally often with both response directions. To evaluate contextual and dynamic intervention effects, ecological momentary assessment (EMA) is measured throughout, with questions about food intake, hunger, stress, emotions, eating intentions, food craving and impulsivity twice a day. Additional EMA preintervention and postintervention measures are administered before and after the intervention phase (4 days each) with a 1-day follow-up EMA 4 weeks after the intervention. Multilevel models will examine the temporal covariance between approach bias and self-reported variables as well as short-term and long-term intervention effects on approach bias, food intake and craving.

**Ethics and dissemination:**

The study was approved by the Ethics Committee of the University of Salzburg. Results will be published in peer-reviewed scientific journals and presented at scientific conferences.

**Trial registration number:**

German Clinical Trials Register DRKS, registration number DRKS00030780.

Strengths and limitations of this studyThe study is a randomised controlled trial testing an m-health intervention to assist participants in implementing their dietary intentions through repeated use of a mobile approach-avoidance intervention compared with a closely matched active control task.It includes ecological momentary assessment (EMA) before, during and after the trial in both control and intervention groups, which allows examining both short-term and long-term intervention effects.It measures a range of potentially relevant phenomena like food craving, hunger, emotions, stress and day-level impulsivity.Control group data allow examining variability in approach bias and its covariation with data obtained through EMA.Measures of food intake are restricted to single-item daily self-reports which are prone to under-reporting and experimenter demand.

Humans make several decisions per day about whether, what and how much to eat.^1^ All these decisions have an influence on human health, as overeating can lead to obesity and related diseases.^2^ It is therefore important to understand which factors contribute to eating decisions and how we can intervene on them. Traditional psychological models have postulated that people reflect on behavioural options, form intentions and then translate these into behaviour. However, decades of research have shown that intentions are often not successfully enacted, a phenomenon termed the ‘intention behaviour gap’.^3^

To investigate why people sometimes fail to transfer their intentions into behaviour, researchers have devised a range of indirect measures, typically assessed with computer tasks based on the measurement of reaction times (RTs),^4 5^ as opposed to direct measures such as self-reported evaluations of stimuli. Under certain conditions, such indirect measures of food preference can increase prediction accuracy of actual behaviour, above and beyond questionnaire data^6 7^ (but see^8^ for a critical discussion). One example of such an RT task is the Approach Avoidance Task (AAT). In the AAT, participants usually use a joystick (or in more recent studies, a touch-screen^9 10^) to perform movements towards or away from different stimulus categories. These categories, such as foods and non-food objects, are compared on how fast they are approached and avoided, and this RT difference is termed the ‘approach bias’.^11^ Here, we adopt an operational definition, such that we define approach bias as the relative speed with which one can approach the target stimuli (eg, foods) in the AAT, remaining agnostic to what might be the underlying mental construct.^8 12 13^ Food approach biases seem relevant to real world eating behaviour, as they have been found to be higher in people who strongly crave foods,^14^ and they relate to increased food consumption in impulsive individuals and in people who are prone to external or emotional eating^15 16^ (but see Spruyt *et al*^17^ for contradictory findings from the alcohol domain and a wider discussion in Friese *et al* and Kakoschke *et al*^18 19^).

So far, it has mostly been ignored that approach biases may fluctuate over time. In most studies to date, approach bias has, at least implicitly, been treated as a relatively stable, trait-like phenomenon, in line with its conceptualisation as a (stable) mental construct. Approach bias is typically measured at a single time point and then correlated with other phenomena like trait food craving,^10^ weight status,^20^ or eating disorder diagnosis.^21^ One recent study demonstrated that approach bias was independent of experimentally induced satiety, indicating stability of the bias across situations. However, participants’ desire to eat specific foods did explain variance in approach bias, implying that bias might vary across time within individuals depending on their current consumption desires.^22^ This is in line with the finding that approach bias for chocolate was positively correlated with current chocolate craving,^23–25^ craving being an experience of intense desire for a specific food which is temporally variable by definition.^26^ Other studies using a mobile version of the AAT indicated that test-retest reliability across eight measurement occasions was low while split-half reliability was high, again indicating temporal fluctuations in approach biases.^27^ This is in line with findings obtained from other indirect measures that showed modest stability over time.^28^ Such within-subject fluctuations in biases are probably not only due to random variation, as approach-avoidance biases have been shown to decrease with after-meal-satiety in normal-weight individuals, and they have been shown to change based on individuals’ current affective states.^29–33^ In combination, these results raise questions about the temporal and situational stability of approach biases.

Associations between behavioural approach bias and intake-related variables have led to the development of Approach-Avoidance Interventions (AAIs). Traditionally, it has been assumed that a stable mental construct thought to underlie the behavioural approach bias can be changed by repeatedly pairing unhealthy foods with avoidance and healthy foods (or neutral objects) with approach. This should then affect food intake. How exactly AAIs might work is, however, a matter of current debate. Based on the idea that the behavioural approach bias operationalises learnt associations between appetitive stimuli and approach, some authors argue that the repeated pairing of appetitive stimuli and avoidance weakens or reverses this association through the formation of new associations between stimuli, movement direction, and evaluative properties inherent to approach and avoidance.^23^ Others, however, argue that stimulus value is updated due to a conflict between evaluation and within-task behaviour which then influences intake decisions,^34–36^ or that altered behaviour is due to changed food evaluations, which are caused by cognitive inferences based on task requirements.^37 38^ Independent of what might be the exact working mechanism, earlier studies have shown that the behavioural approach bias,^39^ food choice,^40^ and subsequent food intake^41^ can be altered by AAIs. The evidence in this domain is mixed, however,^42–46^ which might have several different reasons.

First, in some studies participants approach and avoid stimuli based on their category (eg, food vs objects) and in others, based on an irrelevant feature of the stimulus such as the frame colour or orientation. Such task differences may affect participants’ awareness of the contingencies between stimulus and required response, as well as expectations about training effects. As this awareness could increase the effectiveness of the intervention, especially when AAIs change behaviour through cognitive inferences as noted above,^47^ this study uses a relevant-feature AAT/AAI and closely tracks participants’ contingency awareness. Second, the personal relevance of the trained stimuli may differ between interventions, and this may influence effectiveness.^48^ Some interventions specifically try to retrain approach biases to chocolate in individuals reporting high trait-level chocolate craving or consumption,^39^ while other interventions train responses to a preselected set of healthy and unhealthy foods without taking into account if participants actually consume the unhealthy foods or if healthy foods fit to individual needs of the participants (eg, in terms of taste, food intolerances). Third, most studies only deliver a single session of AAI (with Meule et al and Kakoschke *et al*^49 50^ being exceptions), while more sessions might lead to larger effects that would be easier to detect.^51^ Finally, the effectiveness of AAIs might depend on when the intervention is delivered. It is easy to see that interventions might be most fruitful in or just before moments when the risk for unhealthy intake is high.

Smartphone-based AATs and AAIs are interesting for a range of research questions that cannot be answered with stationary computer-based AATs and AAIs. First, smartphones allow easy delivery of AAI to participants during their daily routines. This helps participants to perform the intervention repeatedly, and to bring the intervention temporally and spatially closer to ‘high-risk’ situations in everyday life. Assuming a rather fast decay of intervention effects, the closer proximity offered by the smartphone should enhance intervention effectiveness compared with conducting it on one’s personal computer^52^ or in a laboratory session.^53 54^ Another advantage of repeated intervention through smartphones is the possibility to measure immediate and delayed intervention effects on fluctuating phenomena like food craving. Lastly, smartphones allow to measure bias more easily at any time of the day, and especially at moments when it may be relevant for food consumption. This allows us to examine the temporal and situational variability of approach bias. Combining it with repeated delivery of eating-related questions throughout the day (ie, ecological momentary assessment, EMA) also allows for correlating fluctuations in approach bias with other temporally variable phenomena like food craving, affect and intake.

Several studies have delivered interventions using computer tasks through the internet^52 53 55–57^ and have generally reported good compliance rates and effects on dietary intake. Smartphone-based interventions using similar RT tasks are much rarer and have reported mixed results on key outcomes.^49–51 58^ One of the two studies delivering smartphone-based AAI required participants to tilt the phone to respond, and found positive effects on food choice and approach bias towards unhealthy foods.^50^ The other study found neither day-level nor longer-term effects of AAI using swipe movements, as compared with an EMA-only intervention and a sham training group.^49^ It is important to note that that study did not find any approach bias in participants to begin with which suggests that the swipe movements did not clearly represent approach and avoidance and that the sample size was small. It is therefore unclear to what degree its results can be taken as evidence against the effectiveness of mobile AAI.

One recent AAT variant does not require swiping movements on the touchscreen, but instead requires participants to physically move the phone towards or away from themselves while viewing food stimuli.^27 59–61^ This task has been shown to be a valid tool to measure food approach biases outside the laboratory and to provide relevant information beyond self-report measures.^59^ In addition to RTs, it also yields data on the force of the movements, which might contain relevant information not captured by RTs.^61^

The study presented here sets out to test its effectiveness as an intervention tool for AAI; that is, when it is programmed to pair the foods that a specific participant wants to eat more often with approach, and to pair the foods that a specific participant wants to eat less often with avoidance responses. Specifically, we will study to what degree the intervention can support participants in their goal of changing their eating behaviour. We further examine the reliability and validity of approach bias scores obtained through a phone-delivered AAT. Combining the AAI/AAT with the repeated measurement of related phenomena through EMA allows us to disentangle short-term and long-term intervention effects as well as to investigate whether approach bias covaries with intake-related variables over time.

## Methods and analysis

### Study overview

The study uses a two-arm, double-blind randomised controlled trial conducted with German-speaking participants, and is coordinated at the University of Salzburg, Austria. It compares an active AAI to a sham-training (a measurement Approach-Avoidance Task, AAT) in its impact on eating behaviour, food liking, food craving and food approach bias.

### Participants

Participants will be recruited via university e-mailing lists, social networks, university events and word of mouth. Participants must be between 18 years and 60 years of age, and must not be pregnant or report a diagnosis for an eating disorder. Importantly, participants must have an intention to change their eating behaviour (which they indicate on sign-up), without further specification regarding increased or decreased intake of certain foods or food categories.

To determine the required sample size, we performed a power analysis using pre-existing data from a (so far unpublished) study, where we attempted to change participants' approach-avoidance bias and analysed its change from pre-training to post-training (see online supplemental file 1 for more information). We opted to use this pre-existing data as the structure of the study is similar to the current study and the correlations and noise therein would be more likely to reflect the findings we will observe than would fully simulated data.

10.1136/bmjopen-2022-070443.supp1Supplementary data

First, group-level differences between the pre-to-post effects of sham and active training were removed such that a time-by-group effect size of 0 was achieved. A new effect size was then applied by increasing the post-treatment group mean of the active training participants by a multiple of 16 between 64 and 244, giving effect sizes around *g*=0.5. After this, participants were randomly sampled with replacement such that sample sizes between 80 and 180 in multiples of 10 were achieved. Each combination of sample size and effect size was resampled and tested 200 times. After sampling a set of participants, a multilevel analysis was performed where approach-avoidance bias scores were predicted with fixed predictors of treatment group (sham or active) and time (pretraining or post-training), as well as random effects of time grouped by participant and time grouped by stimulus. The p value of the group by time interaction was recorded. The proportion of p values below.05 was computed to determine the power at each combination of sample size and effect size.

Based on this power analysis, we determined that a medium effect size (*g*=0.50) and a power of 0.80 would require a sample size of about 150 participants. Based on the effect size observed in that other study of *g*=0.56, 150 participants result in a power of about 0.88. A table with all power analysis outcomes is depicted in online supplemental file 2. With an estimated recruitment rate of three participants per week and allowing for recruitment difficulties slowing down the process, we expect data collection to last from November 2022 to roughly January 2024. Data collection continues until 150 participants are reached.

10.1136/bmjopen-2022-070443.supp2Supplementary data

### Materials and procedure

#### Baseline questionnaires

In a web-based questionnaire (see online supplemental file 3), participants give informed consent (consent form see online supplemental file 4) and then indicate their age, gender, nationality, state of employment, highest achieved formal education level, dietary restrictions (vegan, vegetarian, pescetarian, omnivorous, other), height, weight, and possible food allergies or intolerances. Participants identifying as female or diverse are also asked about their menstrual cycle. Further, to assess exclusion criteria, they are asked if they are currently suffering from an eating disorder. This is followed by the stimulus selection (see below for details). Participants then complete the German versions of the following questionnaires: subscales restrained eating and external eating from the Dutch Eating Behaviour Questionnaire;^62^ the Salzburg Emotional Eating Scale;^63^ the Salzburg Stress Eating Scale;^64^ Perceived Self-Regulatory Success in Dieting;^65^ the short version of the UPPS (Urgency; (lack of) Premeditation; (lack of) Perseverance; Sensation Seeking) Impulsivity Scale.^66^

10.1136/bmjopen-2022-070443.supp3Supplementary data

10.1136/bmjopen-2022-070443.supp4Supplementary data

#### Stimuli

We preselected 90 food and drink pictures from the food.pics^67^ and CROCUFID^68^ databases, and from freely available online resources based on typical availability in Austria and Germany as the main recruitment sites. At the beginning of the study, participants rated these 90 images on two scales: ‘In the last three weeks, on how many days have you eaten/drunk this food/drink?’ (recent intake) and ‘In the next three weeks, on how many days would you like to eat/drink this food/drink?’ (intended intake). We select the six foods with the most negative difference between past and intended consumption as ‘increase foods’ (eaten less often than intended). Then, among the foods that were eaten at least on 6 days in the past 3 weeks, we select six with the most positive difference between past and intended future consumption (eaten more often than intended = ‘decrease-foods’). A randomly selected four of these six images are then used in the intervention phase in both groups while the other two were left untrained to test whether the intervention would be specific to the foods used in the task. A random selection of 8 out of a set of 12 images of office items serves as control stimuli. Figure 1 displays the selection of stimuli. The food stimuli were not categorised as ‘healthy’ or ‘unhealthy’, giving participants full flexibility for choosing ‘increase-foods’ and ‘decrease-foods’.

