#### Set-up call

Within a few days of filling out the online questionnaire, a member of the study team contacts participants to schedule a set-up call via phone or a videoconferencing tool. In this call, the member of the research team explains the procedure of the study. They further help participants install the necessary apps onto their smartphone (m-path KU Leuven, 2022; for EMA and the AAT app (The app can be downloaded on Android devices from this address: https://play.google.com/store/apps/details?id=com.eatlabsbg.eatapp)) and then confirm the correct selection of approach and avoidance foods as determined by the rating task. After the call, participants receive a manual for the study via email, which summarises the study procedures and the use of the smartphone applications and includes participants’ individual three-digit identification code as well as contact information of the study team.

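### Decrease-foods are defined by a positive past-minus-intended difference but filled by rank to a fixed six, with no cut-off at zero and no fallback when fewer than six foods qualify

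*Protocol article*

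**What the plan says.** All references are to the protocol article.

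- **Stimuli.** Participants rate 90 images on past and intended days of intake, each over three weeks. For one category: "We select the six foods with the most negative difference between past and intended consumption as ‘increase foods’ (eaten less often than intended". For the other, the pool is first restricted to foods "among the foods that were eaten at least on 6 days in the past 3 weeks". From that pool "we select six with the most positive difference between past and intended future consumption", and the bracket that follows gives the definition: "eaten more often than intended = ‘decrease-foods". Next, "A randomly selected four of these six images are then used in the intervention phase in both groups".
- **Approach-Avoidance Task.** Assessment sessions use six foods per category and 12 objects. Training uses four foods per category and eight objects. In the active arm, the blocks in which food is avoided contain avoid-foods only. The footnote to Table 1 repeats six and six.
- **Participants.** An intention to change eating is required, "without further specification regarding increased or decreased intake of certain foods or food categories".
- **Abstract, Methods and analysis.** "Intervention group participants always avoid foods that they personally want to eat less often".
- **Set-up call.** Staff "confirm the correct selection of approach and avoidance foods as determined by the rating task".
- **Overall intervention effectiveness.** Multilevel models compare intake of the trained foods before and after the intervention between arms. Equivalent models cover craving and approach bias.

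**The concern.** The bracket in Stimuli defines a decrease-food by the sign of a difference. The procedure that fills the category uses only the rank of that difference and always returns six. The two agree only if the participant has at least six foods that were eaten on 6 or more days and that they want to eat less often. Nothing in the eligibility criteria ensures this, and the intake filter shrinks the pool from 90 images to the foods eaten often.

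Where the two disagree, the list is completed with foods the participant wants to keep as they are or eat more. In the active arm these foods can then be paired with avoidance, although the abstract says that avoided foods are always ones the person wants to eat less. The decrease-food models make no distinction among trained foods, so a fall in intake or craving for such a food counts towards the intervention effect. At stake is what the decrease-food contrasts mean: the introduction gives the aim as helping participants reach their own eating goals, and for these foods a fall is not their goal.

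**Working it through.** The document gives no figure for how many selected foods meet the definition, so there is nothing to reproduce. The check is to follow the rule as written.

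**Step 1: can the rule return a food that fails the definition?** Take an invented participant with eight foods eaten on 6 or more of 21 days:

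| Food | Past days | Intended days | Past − intended |
|---|---|---|---|
| A | 18 | 10 | 8 |
| B | 15 | 9 | 6 |
| C | 12 | 12 | 0 |
| D | 10 | 10 | 0 |
| E | 8 | 8 | 0 |
| F | 6 | 6 | 0 |
| G | 7 | 10 | −3 |
| H | 6 | 9 | −3 |

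The six highest differences are 8, 6, 0, 0, 0, 0. Four of the six decrease-foods are ones this person wants to leave unchanged.

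**Step 2: does such a food reach training?** Four of the six are drawn at random (Stimuli). Let k be the number of selected foods with past above intended intake.

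- P(at least one trained food fails the definition) = 1 − C(k,4)/C(6,4), with C(6,4) = 15.
- Expected number of such trained foods = 4(6 − k)/6.

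| k | Probability | Expected number of 4 |
|---|---|---|
| 6 | 1 − 15/15 = 0 | 0 |
| 5 | 1 − 5/15 = 0.67 | 0.67 |
| 4 | 1 − 1/15 = 0.93 | 1.33 |
| 3 | 1 − 0/15 = 1.0 | 2.0 |

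For k below 3 the probability stays at 1.0 and the expected number rises further.

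**Step 3: how often is k below six?** The document does not say. To show how wide the answer is, assume that M foods pass the intake filter and that each is independently wanted less with probability q. Both inputs are assumptions. The chance that fewer than six qualify is P(Binomial(M, q) ≤ 5):

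| M | q = 0.5 | q = 0.7 | q = 0.9 |
|---|---|---|---|
| 8 | 0.855 | 0.448 | 0.038 |
| 10 | 0.623 | 0.150 | 0.002 |
| 20 | 0.021 | <0.001 | <0.001 |

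The result runs from most participants to almost none, so frequency cannot be settled from the text.

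**Step 4: does another section repair it?** The set-up call confirms a selection. It gives no criterion for rejecting a food and no rule for replacing one. The fixed counts in the task description and in Table 1 leave no visible room for a shorter list.

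**The case against.** The strongest reply is that the sign is stated. Both categories carry it in brackets, and the ranking is described as most positive and most negative. That stands against anyone who infers that the protocol has no sign requirement at all: the intended sign is clear. What is missing is an operative cut-off, and a rule for when the definition and the count of six cannot both be met.

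A second reply is that the set-up call would catch a misassigned food, and that Figure 1 or the preregistration, neither of which is shown, may contain the rule. Either is possible. But the call is described as confirming what the rating task determined, and the article presents its selection rule in full enough terms to conflict with its own abstract. This is more than an omitted detail.

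Several stronger readings are not supported:

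- **A quantified power loss.** A reader might scale down the stated effect of g = 0.50 and its power of 0.80. That would need a share of non-qualifying foods that the document does not give. It would also have to be worked over the four trained foods in the main models. The stated power concerns approach bias, not intake or craving. Zero effect on non-qualifying foods would have to be assumed as well, yet some mechanisms described in the introduction do not need a wish to eat less.
- **One food on both lists.** The assessment blocks show 24 images once each, and 6 + 6 + 12 = 24. This presumes separate sets.
- **The same fault for increase-foods.** These are ranked over all 90 images without an intake filter, so a wrong sign is unlikely.
- **Bias between arms.** Selection follows the same rule in both arms, so no imbalance follows from it.

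**Conclusion.** The point holds as an internal conflict. The definition of a decrease-food and the fixed count of six cannot both be met when fewer than six frequently eaten foods have past above intended intake, and the article does not say which gives way. Followed as written, the rule can train active-arm participants to avoid foods they do not want to reduce, against the abstract, and the main intake and craving models would then credit a fall in those foods as success.

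The size can be given only conditionally. With 5, 4, or 3 or fewer of the six qualifying, the chance that training includes at least one non-qualifying food is 0.67, 0.93 or 1.0. This assumes only that four of six are drawn at random, as stated. The number of participants affected is unknown, and so is any effect on power. The matter is worth correcting because it bears on the meaning of a main contrast and because the ratings needed to deal with it are already collected.

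**What to change.** **Selection.** Reconcile the definition with the fixed count. Make past above intended intake an explicit condition for decrease-foods, and state what happens when fewer than six foods meet it, for example fewer foods, replacement by a set rule, or exclusion. The choice must fit the split into four trained and two untrained foods, the 16-trial training blocks and the 24-image assessment blocks, so it takes more than one added line in the selection script.

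**Analysis, for all participants including those already enrolled.**

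- Flag each selected food by the sign of its baseline past-minus-intended difference.
- Report the qualifying share by arm.
- Run the intake and craving models on sign-consistent foods alongside all selected foods, and name in advance which is the main analysis.

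This does not break randomisation. The allocation may be generated around the time of the questionnaire, but the ratings come before any training and the trial is described as double-blind, so the flag cannot depend on the intervention.

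**Cost.** The analysis needs one flag and one further model fit per outcome. Some participants will contribute fewer foods to the restricted analysis, and precision will fall slightly.
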